## Discussion

4.

The correlation between surgical timing and long-term neurodevelopmental outcomes in children with complex CHD has not been fully studied. Moreover, currently, there is no consensus regarding the optimal surgical timing for neonates with complex CHD. Our study will allow us to define the optimal time-window within the neonatal period to perform cardiac surgery to reduce postoperative morbidity (i.e., postoperative complications) and optimize the neurodevelopment of infants with complex CHD. We hope our work will facilitate the evaluation of the risk/benefit ratio of the chosen therapeutic strategy.

A better understanding of the mechanisms underlying neurodevelopmental disorders in this population will allow the identification of other modifiable risk factors and the development of new prevention and screening strategies to improve the neurodevelopment and overall health of children and adults.

An added challenge for this field is the recruitment of patients with various types of CHD to define a general optimal age for cardiac surgery and an optimal age for each CHD type and not only for TGA and HLHS, which have been studied in more depth.

Moreover, the patients in our study will receive a neurodevelopmental follow-up at 4 months, 12 months, and 24 months. They will benefit from early screening for neurodevelopmental disorders with an orientation toward adapted rehabilitation structures, thereby supporting improvements in their overall neurodevelopmental outcome. The aim is to extend this treatment process to all patients with complex CHD who undergo surgery in their first weeks of life. This project, initially internal in hospitals in Marseille, could be extended with the collaboration of pediatric cardiology and neurology teams across France.

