Neurological	• Ischemic cerebrovascular accident • Hemorrhagic cerebrovascular accident	• Epileptic seizure • Cerebral thrombophlebitis
Surgical	• Recurring diaphragmatic paralysis/paresis • Definitive AV block with device • Acute hemorrhaging requiring revision surgery	• Cardiac tamponade • Unplanned revision surgery • Chylothorax

There is no consensus regarding the optimal age for surgery in terms of morbidity and neurodevelopmental outcomes, and its definition is a real challenge. Importantly, at the present time, there are no established rules for determining the timing of surgery in our department. For the most common CHD types, the TGA are corrected during the first ten days of life. There is a more pronounced degree of variation for HLHS. This common practice won't be changed for our observational study.

Our aim is to determine the relationship between surgical timing and long-term neurodevelopmental outcomes for various types of complex CHD. Similarly to Anderson et al. (15) with postoperative morbidity, we aim to determine a cut-off point for surgical timing that will improve neurodevelopmental outcomes. For each type of CHD, we aim to determine a cut-off for surgical timing based on postoperative morbidity and neurodevelopmental outcomes. We hope that our findings will contribute to the development of surgical timing guidelines in the future.

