### Inclusion criteria

2.2.

In this study, we will recruit infants aged 2 months or less with complex CHD requiring surgery with extracorporeal circulation during their first 2 months of life at the La Timone Enfants Hospital in Marseille. The included patients should be born full-term (at more than 37 weeks). The eligible complex CHDs correspond to the anatomical classification of Clancy et al. (19), (Table 3).

**Table 3 T3:** Classification of complex congenital heart diseases selected for the study, according to Clancy *et al*. (19).

Classification Number	Anatomic Classification (10)	Complex CHD
I	Two-ventricle heart without arch obstruction	TGA with intact ventricular septum
		TGA/VSD
		Tetralogy of Fallot/PA
		Truncus Arteriosus
		TAPVR
II	Two-ventricle heart with arch obstruction	TGA/VSD/CoAo
		VSD/CoAo
		VSD/Interrupted aortic arch
III	Single-ventricle heart without arch obstruction	Unbalanced AVCD
		Tricuspid atresia
		Mitral atresia
		Heterotaxy
		Double-outlet left ventricle
		Double-outlet right ventricle
		Single ventricle (other)
IV	Single-ventricle heart with arch obstruction	HLHS

PA, Pulmonary Atresia; AVCD, Atrioventricular Canal Defect; VSD, Ventricular Septal Defect; CoAo, Coarctation of the Aorta; HLHS, Hypoplasia of Left Heart Syndrome; TAPVR, Total Anomalous Pulmonary Venous Return; TGA, Transposition of the Great Arteries.

For all patients, we must obtain informed consent from both parents (except in special cases justifying consent from just one parent) or from legal representative(s). The parents or legal representatives must be able to read and speak French. Additionally, the included patients will need to be affiliated with French social security.

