#### Sample size

3.1.1.

Two previously published studies that reported a significant correlation between age at surgery and the incidence of WMIs included 26 and 37 patients, respectively (7, 8). Based on the active file of patients with complex CHD operated on each year in Cardiac Surgery at the La Timone Enfants Hospital, the total number of subjects included will be 100. With this number of 100 included patients and according to the values of (i) a 5% bilateral alpha risk and (ii) 80% statistical power, we estimate the minimum correlation coefficient between age at surgery and Bayley-IV test scores as 0.39.

According to the same hypotheses (5% bilateral alpha risk and 80% statistical power), and based on the intended number of patients recruited for each (Clancy) CHD subtypes, the minimum correlation coefficient that could be highlighted between age at surgery and Bayley-IV test scores is:
*r* = 0.38 for class I, two-ventricle heart without arch obstruction (*n* = 50)*r *= 0.65 for class II, two-ventricle heart with arch obstruction (*n* = 15)*r* = 0.76 for class III, single ventricle heart without arch obstruction (*n* = 10)*r* = 0.53 for class IV, single ventricle heart with arch obstruction (*n* = 25)”

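### For TGA, unchanged practice limits the evidence to about the first ten days of life, yet the article promises an optimum within the neonatal period and uses an effect measure that depends on the spread of ages

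*Protocol article*

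**What the plan says.** The Introduction describes current timing at the centre. For TGA, "the TGA are corrected during the first ten days of life". For hypoplastic left heart syndrome, "There is a more pronounced degree of variation for HLHS". It adds that "there are no established rules for determining the timing of surgery in our department", and then that "This common practice won't be changed for our observational study". Eligibility is wider: infants "requiring surgery with extracorporeal circulation during their first 2 months of life".

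Main analysis (3.1.2) estimates a Pearson or Spearman correlation between age at surgery in days and the Bayley-IV scores, with a 95% CI, for the whole cohort and separately by type of heart disease. The stated purpose is to find the best age for each type. A ROC curve with Youden's method supplies the age threshold.

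Sample size (3.1.1) gives a minimum detectable r of 0.38 "for class I, two-ventricle heart without arch obstruction" (n = 50), at "a 5% bilateral alpha risk and (ii) 80% statistical power".

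The Discussion then says: "Our study will allow us to define the optimal time-window within the neonatal period to perform cardiac surgery". The Limitation section lists the single centre, heterogeneity and the total of 100. It still names TGA as a lesion whose timing may be defined, because it recruits frequently. The Conclusion expects the results to help develop timing guidelines. None of these three sections mentions the narrow TGA age range as a limit.

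**The concern.** An observational study that leaves practice alone can inform only about the ages at which that practice operates. The neonatal period is taken here as 28 days. If TGA surgery stays within about ten days, the rest of that period is nearly empty for this lesion. One contrast that the Introduction uses as motivation, arterial switch after two weeks of life, would be almost absent from the cohort.

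The choice of effect measure adds a second difficulty. A correlation mixes the effect per day with the spread of days, so the same loss per day of waiting gives a smaller r where ages are tightly grouped. Because the analysis is run by lesion and HLHS timing is said to vary more, the coefficients for the two lesions are not on a common scale.

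Two misreadings are at stake in a study meant to feed guidelines. A cut-off found inside ten days could be presented as the optimum for the whole neonatal period. A weak TGA correlation could be taken as a sign that timing matters less in TGA.

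**Working it through.** **Inputs from the article.** TGA ages of about 0-10 days (Introduction); r = 0.38 at n = 50 for class I, two-sided alpha 5%, power 80% (Sample size); Bayley-IV SD 15 (section 2.8.2, the scale's normative value).

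**Assumptions.** Ages spread evenly over the range; cohort SD equal to 15; a 28-day range as comparator, because no lesion's range is given in days other than that of TGA. Class I also contains other lesions, so 0.38 at n = 50 is not a TGA figure, and no TGA count is given.

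**1. The plan's own figure.** Fisher z: r = tanh((1.960 + 0.842)/√(50 − 3)) = tanh(0.409) = 0.387. With a t-based critical value and bias correction it is 0.384. The stated 0.38 is reproduced to rounding.

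**2. What r = 0.38 means in points per day.** The SD of an even spread over width w is w/√12, and slope = r × 15/SD(age).

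| Age range | SD of age | Slope for r = 0.38 |
|---|---|---|
| 10 days | 2.89 | 5.7/2.89 = 1.97 points/day |
| 28 days | 8.08 | 5.7/8.08 = 0.71 points/day |

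Over ten days, 1.97 points/day is about 20 points.

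**3. The same effect in a narrower range.** Hold the slope and residual SD fixed, with u = 10/28 = 0.357. Then r' = r·u/√(1 − r² + r²u²) = 0.136/√(0.856 + 0.018) = 0.145. A correlation of 0.38 over 28 days becomes about 0.15 over ten. At n = 50, power falls from about 80% to about 17%. At an assumed n = 30 it is about 12%.

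**4. Precision inside ten days.** Slope needed for 80% power, using the t-based detectable r:

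| n | Detectable r | Points/day | Over ten days |
|---|---|---|---|
| 50 | 0.384 | 2.0 | 20 |
| 30 (assumed) | 0.487 | 2.5 | 25 |
| 20 (assumed) | 0.582 | 3.0 | 30 |

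**5. Can the planned tools place an optimum outside the data?** Youden's method chooses among cut-offs within the observed ages. It also returns one when there is nothing to find: in 2,000 simulated data sets (n = 50, ages evenly drawn from days 1-10, no age effect, 30% delayed), the chosen day was spread almost evenly, with each day selected 179 to 227 times. A correlation does not locate an optimum at all. With a simulated inverted-U effect centred on day 5 of a 0-10 day range, Pearson's r was about 0.

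**The case against.** A reader might infer that the study can say nothing about the timing of TGA surgery. The documents do not support that. The hypothesis is that earlier surgery protects, and the Introduction models its aim on an earlier TGA study whose cut-off, before the third day of life, lies inside days 0-10. That contrast remains available, and the obstacle there is precision. Ten days is also a habit: the centre has no timing rules, the Introduction notes that low weight or instability can delay surgery, and eligibility runs to two months. Some later operations may occur.

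A reader might also infer that the correlation sets the threshold, or that TGA is the commonest lesion in the cohort. Neither is shown. The threshold comes from ROC/Youden, and the Introduction only places TGA among the most common types.

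Three further points on the other side are fair. No comparison of r between lesions is planned, and each r carries a confidence interval. Section 3.1.3.4 already plans adjusted regression coefficients for age with 95% CIs. The article calls the work preliminary.

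These narrow the point without removing it. The regression is a secondary moderator analysis, is not said to be fitted by lesion, and uses standardized coefficients to judge relative importance; those also depend on the spread of ages. Section 3.1.2 sets out to find an age for each type, so readers will see the by-lesion coefficients side by side whether or not a formal comparison is planned. The Limitation section attributes the limit to recruitment and names TGA as answerable, when the Introduction describes TGA timing as narrow.

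**Conclusion.** The point holds in a limited form. If practice follows the Introduction, inference for TGA is confined to about days 0-10, and the Discussion and Limitation go further than the data can. These sections must be reconciled with the Introduction.

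The by-lesion correlation is not comparable across lesions with different age spreads: 0.38 corresponds to about 2.0 points per day over 10 days and 0.7 over 28. A small r in TGA would not be evidence that timing matters less there. Comparisons within ten days remain possible but are imprecise: 80% power needs about 20 points across the range at n = 50, and more with fewer TGA infants.

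These sizes rest on evenly spread ages, a Bayley SD of 15 and an illustrative 28-day comparator. The direction of the effect on r needs only that the slope and residual spread be the same in both ranges. The design is not invalidated; what needs changing is the reporting of the main analysis and the scope of the conclusion.

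**What to change.** - **Section 3.1.2:** beside r, report for each lesion group the slope (Bayley points per day of age at surgery, 95% CI) and the observed age-at-surgery range. Base any statement across lesions on slopes.
- **Sections 4 to 6:** limit any optimal age or cut-off to the ages observed in that lesion, for example its 5th to 95th centile, and reconcile the text with the Introduction's account of TGA practice.
- **Section 5:** add the restricted TGA age range to the limitations.

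This needs no new data, only a simple additional regression by lesion and changes of wording. The downside is a narrower claim for TGA.

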## Limitation

5.

As Complex CHD are characterized by their heterogeneity, the monocentric nature of our protocol study may be considered a limitation, as well as the relatively low number of participants to be recruited (*n* = 100). This preliminary work may allow us to define an optimal surgery timing only for those CHDs that recruit frequently (e.g., TGA, aortic arch hypoplasia). The extension of this project to other pediatric cardiology and neurology teams in France will enable more reliable results to be obtained.

## Conclusion

6.

We will conduct a preliminary observational study to determine the most appropriate surgical timing for each type of complex CHD. This project aims to determine whether an earlier surgery would be a beneficial neuroprotective strategy to reduce brain injuries and postoperative morbidities and improve neurodevelopmental outcomes. This research should be useful in developing guidelines for optimal surgical timing for complex CHDs in the near future. Based on the balance between benefit and risk, these guidelines will make it easier to determine the optimal surgical timing for a newborn or infant with a complex CHD. Secondly we will conduct an interventional study to reduc the age at surgery.
